### Objectives

The primary aim of this study is to evaluate the feasibility and acceptability of an intervention that combines an economic intervention with a self-regulation intervention among adolescents living in urban poverty in Bogotá (Colombia), Kathmandu (Nepal) and Cape Town (South Africa). This will be done by assessing the following criteria (which have been defined as progression to full trial criteria): (1) fidelity across intervention arms; (2) participants attending sufficient intervention sessions; (3) reported adverse events across intervention arms compared to control arm; (4) reported negative experiences related to cash transfers, as well as qualitative perspectives on acceptability of interventions; (5) baseline differences in demographic variables across arms for adequacy of randomisation; (6) adequacy of masking; (7) missing values on outcome instruments; (8) loss to follow-up across timepoints. Furthermore, we aim to evaluate the sensitivity to change on study participants’ clinical and non-clinical outcomes. The study is part of the ‘Improving Adolescent mentaL health by reducing the Impact of poVErty (ALIVE)’ project, which has been introduced elsewhere [12].

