#### Outcome instruments for adolescents

The Patient Health Questionnaire (PHQ-9) Adolescent version (PHQ-A) [34] and Generalised Anxiety Disorder Scale (GAD-7) are the primary outcomes for a future adequately powered trial [35]. They will be assessed using the Measurement of Mental Health among Adolescents and Young People at the Population level Tool (MMAPP) [38], which has the ability to generate equivalency scores for the PHQ-A and the GAD-7. Cut-offs for the PHQ-A and the GAD-7 were previously validated in Nepal, and validations were conducted for Spanish in Colombia and English in South Africa as part of the ALIVE formative work. Based on these validations, cut-off thresholds were selected that minimised false positives. This is because the target group of the intervention is adolescents who do not have depression or anxiety. Sensitivity (and associated false negatives) was less pertinent to selection. (See Table 5 for country-specific cut-offs). The future primary outcome for the full RCT will be defined as the cumulative incidence of depression or anxiety, that is, scoring above depression and/or anxiety cut-offs at one or more of the follow-up assessments.

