**Feasibility of the study procedures**				
Feasibility of randomisation	Difference in participant recruitment rate between arms	1. > 60% participants agree to be (i) re-screened to determine eligibility for the pilot, or (ii) enrolled into the pilot (when second screening for pilot does not take place) 2. > 30% difference in recruitment rate between arms	1. > 60% participants agree to be (i) re-screened to determine eligibility for the pilot, or (ii) enrolled into the pilot (when second screening for pilot does not take place) 2. 20–30% difference in recruitment rate between arms	1. > 60% participants agree to be (i) re-screened to determine eligibility for the pilot, or (ii) enrolled into the pilot (when second screening for pilot does not take place) 2. < 20% difference in recruitment rate between arms
Feasibility of masking research assistants	Self-report questions at the end of each assessment	> 50% guess correct arm	35–50% guess correct arm	< 35% guess correct arm
Feasibility of data collection	Proportion of missing items on the GAD-7 and PHQ-A items at 18 month follow-up	> 20% missing	10–20% missing	< 10% missing
Feasibility of retention	Proportion of recruited adolescents lost to follow-up (LTFU) at 18-month follow-up	> 30% LTFU	20–30% LTFU	< 20% LTFU

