#### Sensitivity to change analyses on participants outcome data

All outcome analyses will take a sensitivity to change approach. This will include descriptive analyses of the cumulative incidence of depression/anxiety (binary outcome), as well as analyses of change on other outcomes using linear mixed models. All results aim to inform a future definitive trial (event rates and effect sizes, respectively), for outcome selection and sample size calculations.

The primary comparison of interest for the adolescent in a future adequately powered trial is the difference in cumulative incidence rate of depression and anxiety throughout the study until 18 months post-baseline (i.e. proportion of adolescents per arm who score above the depression and/or anxiety cut-off at any one of the follow-up time points). We selected this measurement strategy as it takes into account the episodic nature of depression and anxiety. In addition, a point incidence rate at a single time point, such as 18 months, would miss those who developed depression or anxiety along the way but who are not suffering from either depression and/or anxiety at 18 months post baseline, and would result in lower rates, which will make achieving power for a larger trial more difficult. Exploratory analyses (e.g. based on latent class analysis) can be based on “persistent” depression or anxiety, operationalised as 2 or more time points above cut-off among the T1, T2 and T3 follow-up timepoints. For the pilot trial, we will run descriptive comparisons of cumulative incidence between the arms, while not testing for statistical differences. We hypothesise that the cumulative incidence rate will be higher in the control arm when compared to the intervention arms.

For secondary outcomes of a future adequately powered trial, we will explore the difference in change in each outcome within each trial arm from baseline to each follow-up using linear mixed effects regression models (i.e. assessment of *sensitivity to change*). No formal between group statistical testing will be conducted as this pilot cRCT is not designed to detect effects. Given the small number of clusters (or schools) per arm (*n* = 2), the models will include fixed effects of timepoint and school [74]. For each outcome, we will present the model-predicted means and corresponding 95% confidence intervals for each trial arm and timepoint. 

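### Table 7 scores retention at 18 months only, although Objective 8 and the intended cumulative outcome cover all three follow-ups, so a green score sets no limit on loss at T1 or T2

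*Protocol article*

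**What the plan says.** The Objectives of the protocol article list eight criteria, "which have been defined as progression to full trial criteria"; the eighth is "loss to follow-up across timepoints". In Table 7 the retention row uses the indicator "Proportion of recruited adolescents lost to follow-up (LTFU) at 18-month follow-up": green below 20%, amber 20–30%, red above 30%. The data-collection row is tied to the same visit: "Proportion of missing items on the GAD-7 and PHQ-A items at 18 month follow-up". No row sets a limit on loss at T1 or T2.

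Under Outcome instruments for adolescents, the full trial's primary outcome is cumulative incidence, that is "scoring above depression and/or anxiety cut-offs at one or more of the follow-up assessments". The section on sensitivity-to-change analyses repeats this as the proportion who "score above the depression and/or anxiety cut-off at any one of the follow-up time points". It also explains why one late visit was not chosen: "a point incidence rate at a single time point, such as 18 months, would miss those who developed depression or anxiety along the way".

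**The concern.** The Objectives and Table 7 describe the same progression criterion differently, and Table 7 is the decision rule. The visit it scores is also not enough for the outcome that the pilot is meant to prepare. A participant seen at T3 but missed at T1 and T2 counts as retained. If T3 is negative, that participant's cumulative status is unknown. The protocol's own argument against a single 18-month measurement applies equally to a single 18-month retention check.

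Green means that the full trial may proceed with no adaptation. A pilot should show whether its intended primary outcome can be ascertained with the planned visit schedule. As written, the row cannot show this when visits are missed intermittently.

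**Working it through.** The green limit is a chosen cut-off, so there is no formula to reproduce. The surrounding counts agree: 4 × 60 = 8 × 30 = 240 planned per country, and 160 + 229 + 239 = 628 enrolled. The largest T3 losses that still score green are 31/160 (Colombia), 45/229 (Nepal), 47/239 (South Africa) and 125/628 (all sites).

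**Inputs.** From the documents: three follow-ups and the 20% green limit. Assumed, because the documents give neither: the loss d at each visit, and how far misses at different visits fall on the same participants.

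**Share missing at least one of T1–T3, same d at each visit**
- Permanent loss, complete overlap: d
- Independent misses: 1 − (1 − d)³
- No overlap: 3d

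| d | Permanent | Independent | No overlap |
|---|---|---|---|
| 10% | 10% | 27.1% | 30% |
| 15% | 15% | 38.6% | 45% |
| 19.9% (green) | 19.9% | 48.6% | 59.7% |
| 20% (limit) | 20% | 1 − 0.8³ = 48.8% | 60% |

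For partial overlap, a simulation with an exchangeable latent-normal model at d = 20% gives about 43%, 39%, 34% and 28% for latent correlations of 0.3, 0.5, 0.7 and 0.9.

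**T1 and T2 worse than T3.** With 30% missed at T1 and at T2 and 19.9% at T3, the row is still green. The share missing at least one visit is at least 30% and at most 79.9%. Under independence it is 1 − 0.7 × 0.7 × 0.801 = 60.8%.

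**Status undetermined.** One positive visit already makes a case, so the narrower quantity is no observed positive and at least one missed visit. If visits are independent with probability p of scoring positive at each, this share is (1 − (1 − d)p)³ − ((1 − d)(1 − p))³. At d = 20%:
- p = 10%: 0.92³ − 0.72³ = 0.779 − 0.373 = 40.5%
- p = 15%: 0.88³ − 0.68³ = 0.681 − 0.314 = 36.7%
- p = 20%: 0.84³ − 0.64³ = 0.593 − 0.262 = 33.1%

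The values of p are also assumptions.

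**The case against.** The best defence is that the last visit is normally the worst. If adolescents who leave do not return, anyone present at T3 was present before, and scoring T3 alone is conservative. That is correct for permanent loss. Intermittent loss is made less likely by the three-week window at each follow-up and by the option of assessment at home, so one absence from school is not a missed visit. Neither provision guarantees that loss is permanent, and the row does not test it. Objective 8 could also be read as saying what will be examined, with Table 7 fixing the scored visit. But the Objectives call the eight items the progression criteria themselves, so the two texts still need to be aligned.

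Three stronger readings are tempting, and the documents do not support them.
- A reader might infer that about half the participants will lack the outcome. The 49% requires independent misses at about 20% per visit, and it counts incomplete follow-up, not unknown status.
- A reader might infer that the missing-items row also contradicts Objective 8. That row belongs to Objective 7, on missing values, which names no time point.
- A reader might infer that the event rate passed to the sample size calculation will be too low. That needs missed visits to be coded as non-cases, which the protocol never states. Nor is such a bias specific to the choice of visit. With an assumed 12% new-case probability per visit, the true cumulative incidence is 1 − 0.88³, about 32%. Coding missed visits as non-cases gives 0.81 × 0.3185 = 25.8% for permanent 19% loss from T1, against 27.0–27.7% in simulation for independent 19% misses (persistence 0.3–0.5). The handling of missed visits in the estimate can properly be left to the analysis plan.

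Multiple imputation among those followed up may help the outcome estimates. It does not change how the row is scored.

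**Conclusion.** The point holds as an inconsistency in a decision rule. The Objectives and the intended outcome cover every follow-up; the scored indicator covers only the last. Because T1 and T2 are unrestricted, a green score puts no useful ceiling on the share of participants with incomplete follow-up. At an assumed 20% missed per visit, that share runs from 20% (permanent loss) through 49% (independent) to 60% (no overlap). The position within that range depends on an attrition pattern that the documents do not give. If loss proves to be permanent, the present row and a row covering all visits would give the same colour. The change is worth making because it is cheap and the row feeds a progression decision. It does not undermine the pilot.

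**What to change.** Align Table 7 with Objective 8. Apply the existing 20% and 30% limits to loss to follow-up at each of T1, T2 and T3, and let the worst visit set the colour. This closes the gap at T1 and T2 but does not cap the share with incomplete follow-up: just under 20% at every visit still permits up to 59.7%. So also report by arm, as descriptive figures, the proportion assessed at all three visits and the proportion whose cumulative status can be determined. Report missing PHQ-A and GAD-7 items at each follow-up among attenders as well.

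Determinable status should not itself be the scored quantity, because it depends on the outcome. With 19% independent misses and independent visits, 1 minus the undetermined share is about 58%, 63% and 67% at 6%, 12% and 18% caseness per visit. Identical attendance would look better in an arm with more cases, and the protocol expects more in control. The 20% and 30% limits were also set for a different quantity.

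The cost is a change to the Table 7 wording and some extra tabulation; no new data are needed. The stated retention may be less favourable. Enrolment ended in June 2024, so 18-month visits were probably over before publication in June 2026. A change made after data collection should be labelled as such, with the T3-only score shown beside it.

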**Feasibility of intervention**				
Fidelity to ALIVE interventions	Average fidelity across intervention arms, based on Fidelity checklists completed for 10 − 15% of the sessions by trainer/supervisors	< 60% Fidelity	60–75% Fidelity	> 75% Fidelity
Adherence to intervention	Attendance data at each session, as reported on TeamPact	Retention of < 50% of participants through adequate completion of sessions (i.e. > 70%), in each intervention arm	50–70% retention in each intervention arm	> 70% retention in each intervention arm
Presence of (severe) adverse events	Across all active arms compared to control arm	> 20% increase	10–20% increase	< 10% increase
Safety of the cash transfer	Post session feedback from facilitators; Interviews with adolescents and caregivers; (S)AEs	> 30% participants report a negative event	10–30% participants report a negative event	< 10% participants report a negative event

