### Sample size

We aimed to recruit a sample of 240 adolescents (13 − 15 years), living in poor urban households in each country, with an equal sample size in each of the four trial arms (*n* = 60). This study is not powered to evaluate effectiveness [32] but instead aims to test trial procedures, based on which parameters can be defined to run sample size calculations for the adequately powered RCT. We followed recommendations for sample size requirements to estimate key design parameters for pilot trials, which suggest at least 240 measured participants (60 per group) when estimating the Experimental Event Rate [33]. Thus, we aimed to recruit 30 adolescents and their caregivers per school, for a total of 60 adolescents and their primary caregiver per arm.

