#### Assessment of intervention procedures

The study will employ three measures for the assessment of protocol adherence and quality control: (1) competency of facilitators, (2) fidelity to the intervention protocol and (3) attendance by adolescents and caregivers. First, the competency of facilitators will be assessed by trainers/supervisors using the WHO-UNICEF Ensuring Quality in Psychosocial and Mental Health Care Platform (EQUIP) [55]. On the EQUIP platform, competencies for working with children and adolescents will be assessed with the Working with Children Assessment of Competencies Tool (WeACT) [56]. Competencies for working with adult caregivers of the adolescents will be assessed with the 15-item Enhancing Assessment of Common Therapeutic factors (ENACT) tool [37]. The WeACT and ENACT instruments aim to assess common factors in psychological treatments, including task-sharing initiatives with non-specialists across diverse cultural settings. Competencies are assessed while observing culturally adapted, standardised role-plays pre- and post-training, as well as post-intervention, (for all three ALIVE intervention arms) with scoring done by a trained rater or the trainers/supervisors.

Second, the fidelity to intervention protocol will be assessed using self-developed instruments designed to assess the implementation of the ALIVE intervention (all three arms) to intervention protocols. These will be completed by one facilitator at each session, and by trainer/supervisors through observations of approximately 25% of sessions. The assessment of fidelity, as well as other procedures to implement the intervention, was streamlined across the sites (i.e. a joint training of trainers was held, same duration and content of the interventions).

Third, attendance of ALIVE intervention sessions by adolescents and caregivers will be monitored using TeamPact. TeamPact is a mobile app that can be used offline, which helps facilitators collect information on attendance and length of sessions, and allows facilitators to provide feedback on the sessions.

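### Table 7 averages fidelity, and on its plain reading pools adverse events, over the three active arms, leaves mixed adherence uncoloured when read literally, and conflicts with the Methods on the fidelity sample

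*Protocol article*

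**What the plan says.** The Objectives set out to "evaluate the feasibility and acceptability of an intervention that combines an economic intervention with a self-regulation intervention". Table 7 (Criteria for progression to full trial) gives the rules for that judgement, and the Data analysis section calls their assessment the primary analysis. Green means that the trial can go ahead unchanged.

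Three rows under Feasibility of intervention matter here:

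- **Fidelity.** The indicator is "Average fidelity across intervention arms, based on Fidelity checklists completed for" 10–15% of sessions by trainers or supervisors. Red is below 60%, amber 60–75%, green above 75%.
- **Adherence.** Red is "Retention of < 50% of participants through adequate completion of sessions (i.e. > 70%), in each intervention arm". Amber is 50–70% "retention in each intervention arm". Green is "> 70% retention in each intervention arm".
- **Adverse events.** The comparison is "Across all active arms compared to control arm". Red is an increase above 20%, amber 10–20%, green below 10%.

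The section Assessment of intervention procedures says that the fidelity instruments are completed by one facilitator at each session and "by trainer/supervisors through observations of approximately 25% of sessions".

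**The concern.** The question is whether the combined intervention can be taken forward, but the fidelity score mixes that arm with two single-component arms. If the combined arm is delivered poorly and the others well, the row can still say that no adaptation is needed. The adverse-event row has the same weakness if it is pooled. The adherence row has a different one: it gives no verdict when arms fall in different bands, which is the case where a rule is most needed. Separately, two sampling fractions are given for what reads as one supervisor assessment, so the precision of the fidelity score is not fixed. These rules are stated in full as a priori criteria for the primary outcome, so this is not detail that a protocol would leave to a later analysis plan.

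**Working it through.** The arm-level values below are illustrative assumptions. The thresholds are those of Table 7.

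**1. Fidelity (arms weighted equally).** The row is green when (F1 + F2 + Fc)/3 > 75, that is, when Fc > 225 − (F1 + F2), where Fc is the combined arm.

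- Arms at 90, 90 and 50: 230/3 = 76.7%, green, although 50% alone is red.
- Other arms both at 90: green for any Fc above 225 − 180 = 45%.
- Other arms both at 85: green for any Fc above 225 − 170 = 55%.
- Other arms both at 80: green needs Fc above 65%, so a red combined arm cannot score green.
- Limit: a combined arm just under 60% scores green once the others average more than about (225 − 60)/2 = 82.5%.

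**2. Adverse events (equal arms, no excess in the other two).** The pooled excess is e/3.

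- e = 25%: 8.3%, green, where that arm alone would be red.
- e = 50%: 16.7%, amber.
- The row stays green for any e below 30%.

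An example uses the planned size, which the Sample size section gives as 30 per school "for a total of 60 adolescents and their primary caregiver per arm" in each country. Take control 6/60, each single-component arm 6/60 and combined 20/60.

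- Combined arm: 33.3% − 10.0% = +23.3 points (red on the absolute scale).
- Pooled: (6 + 6 + 20)/180 = 17.8%, and 17.8% − 10.0% = +7.8 points (green).
- On the relative scale the same pooled data give 17.8/10.0 − 1 = +78% (red).

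The unstated scale can therefore change the colour by itself.

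**3. Adherence.** Three arms with three bands each give 3 × 3 × 3 = 27 patterns. Read literally, only the 3 patterns with all arms in one band get a colour. Arms at 40%, 60% and 80% get none. The table shows the exact binomial probability of no colour, with independent arms and no clustering. It equals 1 minus the sum over bands of the product of the three arms' probabilities of falling in that band.

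| True adherence in the three arms | n = 60 per arm (one country) | n = 180 per arm (three countries) |
|---|---|---|
| 60 / 60 / 60% | 24% | 1% |
| 70 / 70 / 70% | 74% | 75% |
| 75 / 75 / 75% | 52% | 20% |
| 80 / 80 / 40% | >99.9% | >99.9% |

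**4. Fidelity sample.** Each group has 20 adolescent and 6 caregiver sessions, 26 in all, and there are two schools per arm and country. The number of groups per school is an assumption. About 15 per group and 30 per school suggests two. Colombia enrolled 160/8 = 20 per school, so one is possible there.

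| Groups per school | Sessions per arm and country | 10–15% | 25% |
|---|---|---|---|
| 1 | 26 × 2 = 52 | 5.2–7.8 | 13 |
| 2 | 26 × 4 = 104 | 10.4–15.6 | 26 |

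**The case against.** Several points against this have force.

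- **Adherence.** The each-arm wording can be read as an instruction to colour every arm separately. Then 40/60/80 is red, amber and green, and nothing is missing. That reading is possible, so the defect is ambiguity. A reader might also infer that a combined arm failing on attendance could score green. It cannot: green requires more than 70% in each arm on either reading.
- **Adverse events.** The phrase could mean each active arm against control. Pooling is the plain reading, and no per-arm rule is given, but it is not certain.
- **Consequence.** A reader might infer that the decision on the combined arm would rest on the other two arms. The documents do not support that. The combined arm is a third of the fidelity average, the adherence row binds on it, and the step to a full trial is conditional on all criteria being met. The safety board receives every adverse-event report and can recommend stopping. Supervision, competency assessment and interviews also cover each active arm. None of these is a scoring rule, but they limit the harm.
- **Likelihood.** A reader might infer that the combined arm is the likeliest to have low fidelity because its content was condensed. The protocol says that the content was kept and its sessions are longer (about 2 h against 1.5 h). Nothing shows which arm will do worse.
- **Design choice.** A programme-level average over the ALIVE interventions is defensible as an overall summary. It does not answer the stated primary aim by itself.
- **Sampling fractions.** They could be reconciled if only some observed sessions were scored. The article does not say so and gives no rule for choosing them.

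**Conclusion.** The concern holds, as something that should be fixed. Two parts are firm: fidelity is expressly an average that can turn a red combined arm green, and 25% conflicts with 10–15%. The fidelity masking needs the other two arms to average above about 82.5%. Below that, a red combined arm can still be shown as amber (80, 80 and 59 average 73%).

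Two parts depend on reading. Pooled adverse events would dilute a one-arm excess threefold, assuming equal arms and no excess elsewhere, and the scale of the increase is undefined on any reading. The literal adherence rule leaves 24 of 27 patterns without a colour. The probabilities of no colour rest on assumed true rates and ignore school clustering.

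The documents support saying that the rules do not isolate the combined arm. They do not support saying that the plan would approve a failed combined arm regardless of its results.

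**What to change.** - Give fidelity, adherence and adverse events a colour for each active arm, pooled over countries, with country results descriptive. Keep the a priori overall score beside them. Let the combined arm's colour govern progression of the combined intervention.
- Reword the overall adherence row: red if any arm is below 50%; amber if none is below 50% but any is at 50–70%; green if all are above 70%.
- Express the adverse-event increase as a per-participant risk difference against control.
- Reconcile 25% with 10–15%, and score every observed session.

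This is table wording applied to data already collected by arm. The cost is fewer observations per arm and more chance of an amber or red by chance. That is why arms are pooled over countries rather than taking the worst of nine arm-by-country cells. In a simulation with equal true risk in every arm and no clustering, the worst of nine cells at n = 60 reaches a 10-point excess in about 9%, 32% and 55% of trials at true risks of 5%, 10% and 20%. The worst of three pooled arms at n = 180 does so in under 0.1%, 0.3% and 2.8%. Clustering would raise these figures.

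Timing needs disclosure. Enrolment closed on 26 June 2024, so 18-month follow-up falls around December 2025, before publication in June 2026. If data are already available, the arm-level scoring should be labelled as added after the a priori table.
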